**Summary**

Between 12-30% of patients with severe malaria die despite rapid killing of malaria parasites with antimalarial drugs. This is because malaria parasites have already caused organ/tissue damage Better treatments are needed to reduce this unacceptably high mortality rate. One strategy to reduce mortality is to use adjunctive treatments (ie given in addition to standard antimalarial drugs) that will reduce/reverse the tissue damage caused by severe malaria. We have previously shown that levels of nitric oxide (NO) and its precursor arginine are low in severe malaria. NO production has been associated with protection from severe malaria in multiple human studies, including the NIHRD-MSHR studies in Indonesia. L-arginine is a naturally-occurring amino acid found in plant and animal protein. It is the only substrate for NO production. Levels of arginine are low in both children and adults with severe malaria, and very low levels have been associated with increased mortality. Because NO has multiple anti-disease properties (reducing cytokine-damage, reducing stickiness of blood vessels, reducing apoptosis), a treatment that will return NO levels back to normal in severe malaria, may improve outcome by reducing/reversing the tissue damage already caused by malaria parasites. We propose that by giving arginine in malaria, the low levels of arginine can be corrected and NO production can be returned to normal, allowing NO to reduce tissue and organ damage. Intravenous L-arginine has been used safely in large doses for over 40 years as a diagnostic test of pituitary function. It has also been used in patients with sepsis, coronary artery disease, peripheral vascular disease, sickle-cell vaso-occlusive crisis with improvement in NO production, vascular function and their clinical condition. These studies also show L-arginine infusion to be cheap and virtually free of adverse reactions, even at doses much higher than we will use in this study. **Our goal**is to determine if L-arginine has potential to reduce tissue damage and improve outcome in severe malaria when added to standard quinine therapy. As the first steps, we plan 3 stages over 3 years:

***Stage 1: Natural history study: time course of recovery of hypoargininemia (and pharmacodynamic measures) in uncomplicated and severe malaria***

**Aim:** Stage 1 is designed to determine the natural rate of recovery of L-arginine in patients with uncomplicated and severe malaria. Results will be combined with those from stage 2 to enable us to derive a pharmacokinetic (PK)-pharmacodynamic (PD) model using a computer software program which will accurately describe and predict the relationship between L-arginine plasma concentration and NO concentration both in plasma and urine as well as real time measurements of NO production in lungs and endothelium. This will enable us to determine the optimal dosage of L-arginine which should be given in future studies in malaria.

**Methodology:** We will undertake serial clinical and parasitological assessments on patients with uncomplicated or severe malaria, with serial measurements of blood (total ≤20ml) and urine (for arginine and NO measurements), along with measurement of exhaled NO (a suimple procedure breathing into a tube), endothelial function (non-invasively using an ultrasound method) and lung physiology (non-invasive breathing tests). Stage 1 is strictly observational with no administration of arginine and will be the equivalent to a “zero-dose” of arginine.

**Results:** We expect that there will be significant differences in both the initial levels and rates of recovery of arginine levels in the uncomplicated and complicated malaria and combined with Stage 2 will allow us to decide the optimal dosage and timing of L-arginine supplementation.

***Stage 2: Pilot pharmacokinetic, pharmacodynamic and safety study of arginine in uncomplicated falciparum malaria.***

**Aim:** This study together with stage 1 will allow us to determine the optimal dosage of L-arginine to improve production of NO, and confirm the safety profile of arginine in malaria.

**Methodology:** In a dose-escalation design, patients with *uncomplicated malaria* will receive dose of 3g of intravenous L-arginine, increasing to 6g then 12g (as well as standard quinine). As in stage 1 we will undertake serial clinical, parasitological over 24 hours with serial measures of blood (total ≤25ml) exhaled NO and ultrasound endothelial assessments for PK-PD measurements.

**Results:** We expect that arginine supplementation in malaria will increase NO production and be confirmed to be safe. Combined with stage 1, will allow us to decide the optimal dosage and timing of L-arginine supplementation.

***Stage 3: Randomised concentration controlled trial, safety and PK-PD study in uncomplicated malaria.***

**Aim**: To confirm that the loading and maintenance doses of L-arginine calculated from stage 1 and 2 will increase NO and improve biomarkers of outcome in uncomplicated malaria.

**Methodology**: Patients with *uncomplicated malaria*will be randomized (in addition to standard quinine treatment) to receive either IV L-arginine or saline, to determine if arginine administration results in more rapid return to normal of NO production and more rapid improvement in biomarkers of outcome (including lactate levels), endothelial function, fever clearance time and parasite clearance.

**Results**: We hypothesize that patients receiving L-arginine will have increased measures of NO production, improved biomarkers, and faster fever resolution time. We also expect further confirmation of the safety of L-arginine infusion.

***Expected Benefits:***The results of the first 3 stages will confirm safety of arginine in malaria, and will establish an optimal dose that will increase NO production. We will test if arginine can improve a variety of biochemical and clinical markers of outcome. With the results of the current proposal, we will then be able to proceed to pharmacokinetic-pharmacodynamic studies in severe malaria with a view to a future randomized controlled trial in severe malaria. Arginine is a cheap, safe, natural product. Our longer term goal is to determine if adding arginine to standard antimalarial therapy in severe malaria, can reduce tissue damage and further decrease mortality in severe malaria.

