**Please see Appendix 3 for the types of physiological tests that will be done and where they will be done.**

**Study 2**

***Pilot pharmacokinetic, pharmacodynamic and safety study of exogenous arginine in uncomplicated falciparum malaria:***

*Overview:* In this pilot study in uncomplicated malaria we will generate initial safety, pharmacokinetic and pharmacodynamic data for exogenous arginine administration. We will use a dose-escalation design; all doses (3-12g) will be in the low-mid range of dosages previously used safely in humans (6-30g). *Dosing:* All doses of arginine hydrochloride will be infused intravenously over 30 mins (which is the standard infusion time). Initial dosing will be 3g (n=10), increasing to 6g (n=10), increasing to 12g (n=10) if lack of significant toxicity is demonstrated at each dosing level. Each arginine dose will be added to 100ml normal saline (the standard diluent safely used in other studies) such that total concentration is ≤10% (see CRF)

In addition to arginine, all subjects will be treated with standard antimalarial drugs (currently quinine) as per standard RSMM/Depkes practice/protocols.

*Clinical measures.* Vital signs (pulse rate, BP, temperature, respiration rate), and a standardised clinical assessment (symptom/sign list) will be serially monitored over 48 hours (see table 2). ECG will be monitored from -60 to 240 mins.

*Blood sampling*:

Two venous cannulae will be placed:

A cannula in the right forearm will be used for administration of IV arginine, and for any IV fluids required after arginine administration.

A cannula in the left forearm or antecubital fossa for sampling of venous blood, placed one hour prior to arginine adminstration.

At the time of cannula insertion we will take 7 ml heparinised baseline blood. This will be the -60 minute sample: 60ul will be used for baseline iSTAT EC8+ measurement of electrolytes, glucose, urea, and bicarbonate. The remainder will be processed as per NO Study II SOP for heparinised blood.

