*Interpretation:* Pharmacokinetic models will be fitted to concentration-time and concentration-effect data from studies (a) and (c) using NONMEM (v. 5)51, to provide population parameter estimates, mean parameter values and their between-subject variability where possible. This analysis will include assessment of possible covariate relationships, where parameter values such as clearance may be correlated with patient demographics such as age. A model will be developed that describes the time course of effects of arginine in terms of NO production (plasma NOx/creatinine ratio [systemic NO production] and exhaled NO [pulmonary NO production]), oxidant stress, endothelial function, microvascular flow and gas transfer/physiological deadspace. It is also intended to address biomarkers of effectiveness. **[name] from NIHRD will be invited to the Dept Pharmacy in Brisbane to join the NONMEM modeling for the PK-PD relationships outlined above.**

Safety data from study 2 will be reviewed by an experienced independent data monitoring committee (see appendix) before proceeding to study 3. The pharmacokinetic-pharmacodynamic model developed in study 2 will enable us to predict the dosing and best sampling schedule (both pharmacokinetic and pharmacodynamic) for use in study 3. If the pharmacokinetic-pharmacodynamic model suggests that a higher dose than 12g may be required, a dose of up to 18 g may tested in stage 2 of the study prior to commencing stage 3.

*Potential adverse effects (in study 2 and study 3) and study response:* A number of adverse effects have been previously noted with large *supraphysiological* dosing in subjects with normal plasma arginine levels. These have been infrequent and usually at the standard high dose (≥30g) required to stimulate growth hormone release, **a *dose that will not be used in our studies.*** Arginine is a natural product that has been widely used in subjects with cardiovascular disease, sickle cell disease, and sepsis, with an excellent safety profile. This study primarily examines pharmacokinetic-pharmacodynamic modeling, but will also confirm safety in uncomplicated malaria.

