*d) Consequences of tissue NO production from tissue NOS.* We believe that tissue NO production will have tissue-protective effects and will also reduce generation of superoxide from arginine-deficient NOS. Nevertheless we will be able to detect unexpected deleterious effects of increased tissue NO. As well as the organ-specific biochemical markers above (including creatinine, creatine kinase and liver enzymes/bilirubin), our existing lung function laboratory at RSMM and the exhaled NO apparatus will give us the unique opportunity to relate exhaled NO to measures of pulmonary gas transfer and alveolar dead space, sensitive markers of lung injury.

In the current sickle cell disease trial in the US children with acute vaso-occlusive disease, 36 patients (age 4-18 years) have been randomized to IV arginine 0.1 g/kg vs placebo. This has been very well tolerated, with no significant effect on blood pressure, liver function tests, electrolytes, glucose, renal function or vital signs ([name], personal communication 2004). There have been no serious adverse events, and no acidosis

**Serious adverse events:** The following adverse events will be deemed serious, and will be notified immediately to the Chief Investigators and to the Chair of the Data Monitoring Committee for immediate review:

1. Death
2. Serum K+ rising > 6.0 meq/L with ECG changes
3. Anaphylaxis
4. SBP falling below 80 mmHg unresponsive to saline infusion
5. Clinical requirement for admission to High Care Unit, dialysis or ventilation

The doctor responsible for immediate management of adverse effects will be the internal medicine residents from Manado, currently [name]. These are very experienced senior internal medicine residents.

**Limitations of Study 1 and 2:** Only patients with Hb≥6g/dl are included in this study. We do not believe that the PK-PD relationship will be significantly different in severe malarial anemia than in other forms of severe malaria, but cannot exclude this. Once the PK-PD relationship in severe malaria is known, in future studies we may be able to confirm its similarity in severe malaria anemia with fewer blood draws.

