**Study 3:**

***Randomised concentration controlled trial, safety, and pharmacokinetic study in uncomplicated malaria:***The pharmacokinetic-pharmacodynamic model [from studies 1 and 2)] will be used to determine an appropriate loading and maintenance dose of arginine in uncomplicated malaria, to achieve average plasma arginine concentrations of ~600 uM (a plasma level ~4 times the Km of CAT2 transporters for cellular uptake of extracellular arginine). *Prior to the commencement of study 3, the Data Monitoring Committee will review the dosing and sampling schedule we will calculate from the pharmacokinetic-pharmacodynamic model generated in studies 1-2.* In addition, the target concentration (600 mcM) may need to be readjusted based on the results from studies 1 and 2.

*Design:* Randomised Concentration Controlled Trial.

*Treatment allocation:* Patients with uncomplicated malaria will be randomized to receive one of two treatments:

i) Standard RSMM antimalarial drug regimen for falciparum malaria (currently quinine) plus normal saline placebo (loading dose of 100 ml over 30 mins plus maintenance infusion using same volume in [ii] below).

ii) Standard RSMM antimalarial drug regimen for falciparum malaria (currently quinine) plus IV arginine: loading dose as 30 min infusion (see CRF) followed by maintenance infusion over 12 hours. The doses of arginine will be determined from the pharmacokinetic-pharmacodynamic model to maintain a plasma level of 600uM.

An independent statistician will use computer-generated randomization to generate blocks of patient numbers for each treatment.

*Sample size:* Extrapolating from similar concentration controlled trials, we estimate approximately 20 subjects in each of the two groups. Sample size calculation will require the results of the natural history of arginine/NO/NOx levels during malaria (study 1), and the maximal improvement and time course of improvement following administration (study 2). Therefore the final sample size will be calculated based on the results of studies 1 and 2. The sample size will be reviewed by the Data Safety and Monitoring Committee, and each of the relevant ethics Committees will be notified prior to commencement of Study 3 with confirmation of the number of patients.

*Patient numbering and randomization*:

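### Thirty patients in Study 2 and about 20 in Study 3 cannot confirm that arginine is safe: even with no serious events, rates of up to about 6% pooled and 26% per dose level would remain possible

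*Combined protocol and SAP*

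**What the plan says.** The claim appears in three places.

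- Summary, Stage 2: the aim includes confirming the safety profile, and the expected result is that arginine will be confirmed as safe.
- Summary, Stage 3, Expected Benefits: "The results of the first 3 stages will confirm safety of arginine in malaria". The same paragraph goes on to say that the investigators can then proceed to studies in severe malaria.
- Study 2, Potential adverse effects: "This study primarily examines pharmacokinetic-pharmacodynamic modeling, but will also confirm safety in uncomplicated malaria".

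The patient numbers behind the claim are these.

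- Study 1: "Stage 1 is strictly observational with no administration of arginine".
- Study 2, Dosing: "Initial dosing will be 3g (n=10), increasing to 6g (n=10), increasing to 12g (n=10) if lack of significant toxicity is demonstrated at each dosing level".
- Study 3, Sample size: "we estimate approximately 20 subjects in each of the two groups", one of the two groups being saline. The number is provisional: "Therefore the final sample size will be calculated based on the results of studies 1 and 2".

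Study 2 gives single 30-minute infusions. Study 3 gives a 30-minute load and then maintenance over 12 hours. A further Study 2 level of up to 18 g is possible, with no cohort size given.

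For safety, the plan has per-patient thresholds for stopping the infusion, a list of five serious events, serial bedside chemistry, frequent vital signs, ECG monitoring, and committee review of Study 2 before Study 3. The text available gives no confidence limit, excluded event rate or tolerable rate for adverse events.

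**The concern.** To confirm safety is to say that harm above some level has been ruled out. The plan names no such level, and the number treated sets a limit on what can be ruled out. A clean record in a small group is compatible with a serious reaction that is far from rare.

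The wording matters because of what follows from it. Expected Benefits ties the safety result to the next programme in severe malaria, and the Ethics section says that Studies 1-3 will inform whether that study is warranted. Committees told that safety is confirmed would be told more than the data can show. The Limitations paragraph for Studies 1 and 2 discusses only the exclusion of severe anaemia and does not mention the number treated.

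**Working it through.** The plan gives no safety sample size, event rate or bound, so there is no figure of its own to reproduce.

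**Inputs.** Study 1: 0 on arginine. Study 2: 10 + 10 + 10 = 30. Study 3 arginine arm: about 20. Total: 30 + 20 = 50. The confidence level is my assumption, so I show both one-sided and two-sided 95%.

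**Upper limit when no event is seen.** The chance of no event in n patients at true rate p is (1 − p)^n. Setting this to 0.05 gives the one-sided 95% exact limit, 1 − 0.05^(1/n). Setting it to 0.025 gives the upper end of the two-sided 95% exact interval, 1 − 0.025^(1/n). For n = 10, the one-sided limit is 1 − 0.05^(1/10) = 1 − 0.741 = 0.259.

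| Group | n | One-sided 95% | Two-sided 95% |
|---|---|---|---|
| One Study 2 dose level | 10 | 25.9% | 30.8% |
| Study 3 arginine arm (provisional) | 20 | 13.9% | 16.8% |
| All of Study 2 (three doses mixed) | 30 | 9.5% | 11.6% |
| All arginine patients (regimens mixed) | 50 | 5.8% | 7.1% |

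If an 18 g level were added with 10 patients (cohort size assumed), n = 60 gives 4.9% (6.0%).

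**Chance of a clean record despite a real risk**, (1 − p)^n:

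- true rate 10%, one dose level: 0.90^10 = 0.35
- true rate 5%, one dose level: 0.95^10 = 0.60
- true rate 5%, Study 3 arm: 0.95^20 = 0.36
- true rate 5%, all of Study 2: 0.95^30 = 0.21
- true rate 2%, all 50: 0.98^50 = 0.36

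**Patients needed, all event-free, to exclude a rate at one-sided 95%**, the smallest n with (1 − p)^n ≤ 0.05: 29 for 10%, 59 for 5%, 149 for 2%, 299 for 1%. All of Study 2 (30) just reaches the first. All 50 pooled do not reach the second.

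**The case against.** The best defence is that the plan is more careful than its summary. The Study 2 overview calls the study a pilot giving initial safety data, the Rationale speaks of cautious first steps, and the Study 3 interpretation promises only further safety data. An independent committee reviews Study 2, severe malaria needs a separate ethics submission, Study 3 has a concurrent saline arm, and there are decades of earlier human use.

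Much of this stands as protection for patients, but none of it bounds the event rate in malaria. The plan says that known adverse effects were noted in subjects with normal arginine levels and that the pharmacokinetics are undescribed in low-arginine states such as malaria. The cautious wording elsewhere shows that the document is inconsistent, and the three strong statements remain.

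A reader might infer more than the documents support, in five ways.

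- **That 26% attaches to the confirm-safety claims.** It does not. Those claims concern Study 2 as a whole and the programme, where the limits are 9.5% and 5.8%. The 25.9% belongs to one dose level and bears on the escalation condition, "if lack of significant toxicity is demonstrated at each dosing level", which makes no claim to confirm safety.
- **That zero events will by rule be taken as proof.** No such rule is written; this is an inference from the word confirm.
- **That a non-significant test will be reported as no harm.** No significance test for safety is planned. Miss rates for an assumed shift in a laboratory marker would answer an analysis the plan does not contain.
- **That "Nevertheless we will be able to detect unexpected deleterious effects of increased tissue NO" is a claim about power.** In context it introduces the measurements available: creatinine, creatine kinase, liver enzymes, gas transfer and dead space. I make no point of it.
- **That 6% is the bound for arginine as it will be used.** The pooled figure mixes single infusions of 3, 6 and 12 g with a load plus 12-hour maintenance. For the Study 3 regimen alone the limit is 13.9%.

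The committee appendix that the plan mentions is not in the text available, so I cannot say whether it holds a criterion.

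**Conclusion.** The concern holds as a mismatch between the stated conclusion and the numbers treated. The claim to confirm safety, made for Study 2 and for the programme, is stronger than 30 and about 50 treated patients can support. In the most favourable case, with no serious events, the one-sided limits are 9.5% for Study 2 and 5.8% for the pooled programme; the latter is generous because it combines different regimens. Any observed event would raise them.

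This rests on the planned 30, a provisional 20 in the Study 3 arm, no 18 g cohort, and 95% confidence. The conclusion does not depend on the choice between one-sided and two-sided limits, and an assumed extra cohort of 10 would not change it. The trial remains valid for its pharmacokinetic and pharmacodynamic aims. What changes is what may be said about safety before moving to severe malaria.

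**What to change.** 1. In the Summary (Stage 2, and Stage 3 Expected Benefits) and in Study 2, Potential adverse effects, replace the claim to confirm safety with a statement that the studies will provide preliminary safety data.
2. Report serious and other adverse event rates to the Data Monitoring Committee and the ethics committees by dose level and regimen, each with exact 95% limits, stating whether these are one-sided or two-sided. Mark any pooled figure as mixing regimens, and the Study 3 number as provisional until it is fixed.
3. Report laboratory and physiological safety changes (for example potassium, bicarbonate, glucose, creatinine, enzymes, gas transfer and dead space) as estimates with confidence intervals, set against the saline arm in Study 3.

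The cost is wording and some confidence limits on data already planned. No patients, samples or clinical rules are added. The downside is that the stated safety conclusion will be less favourable.

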**Background**

Please see appendix 1 for the list of abbreviations

**1. Wellcome Trust-NHMRC studies:**

In 2003, NIHRD and MSHR submitted a joint funding submission to The Wellcome Trust (a UK-based medical charity) and NHMRC in response to their call for submissions for their inaugural International Collaborative Research Grants Scheme. The submission was endorsed by the Secretary of NIHRD and the Director of MSHR. Over 140 submissions were received, and these were scrutinized by an international scientific panel for both scientific merit and potential for translation into improvements in health. The NIHRD-MSHR submission was one of only 11 that were successful. There were two components to the submission: The first involved comparative studies of artemisinin combination therapy in Timika, and whether widespread deployment will reduce malaria morbidity and mortality in a medium-transmission region. The ACT comparative studies have been approved by the Ethics committee in Jakarta and the studies have commenced in Timika. The second component of the Wellcome-NHMRC submission is an extension of the NIHRD-MSHR nitric oxide studies. For the first time we will extend the findings from our pathophysiology studies to test whether a simple intervention with arginine, a natural product found in food protein, can increase nitric oxide production and reduce malaria morbidity when used as adjunctive treatment for malaria.

